## Abstract

**Background:**

Physical inactivity is deemed to be the fourth leading cause for premature death. Nevertheless, only a minority of children and adolescents in Germany fulfil the guideline of the World Health Organization of at least 60 min of moderate-to-vigorous physical activity per day. Children and adolescents with a lower socioeconomic background and especially girls are regarded as a high-risk group in terms of physical inactivity. Aim of this study is to examine how a theory-based physical education intervention programme supporting students’ autonomy, competence and relatedness affects physical activity both during these lessons and in leisure time. Based on the self-determination theory and the social cognitive theory, the extent to which autonomy, competence, relatedness, social support and self-efficacy in girls mediate the effect of the intervention programme on their physical activity will be examined. Moreover, the potential moderating role of socioeconomic status, environmental factors, teacher characteristics and BMI will be tested.

**Methods:**

CReActivity is a two-arm cluster randomised controlled trial with a follow-up period of three months after the end of the intervention programme. A total of 600 sixth grade girls in lower secondary schools in Bavaria, Germany will be proactively recruited. The intervention is carried out by the physical education teachers of the participating classes for five months. Primary outcome is the girls’ physical activity measured by accelerometers and systematic observations.

**Discussion:**

We expect to provide an intervention programme that can contribute to the increase of physical activity levels in girls and offer insights into the mechanisms of physical activity behaviour change.

**Trial registration:**

German Clinical Trials Register DRKS00015723 (date of registration: 2018/10/22 retrospectively registered).

**Electronic supplementary material:**

The online version of this article (10.1186/s12889-019-6817-y) contains supplementary material, which is available to authorized users.

## Background

Although it is widely known that physical inactivity is a cause of chronic diseases, such as obesity, type II diabetes, hypertension, cardiovascular diseases, colon and breast cancers, and thus, the fourth leading cause for premature death [1], a high percentage of people in industrialised countries still lead a sedentary lifestyle [2]. According to the Health Behaviour in School-aged Children (HBSC) study, a sedentary lifestyle is already observable at a young age, particularly in girls [3]. A study by Cooper, Goodman [4] analysing pooled accelerometer data from more than 27,000 children and adolescents (aged 3 to 18) shows that only 9% of the male and 2% of the female participants meet the World Health Organization (WHO) recommendation of daily 60 min moderate-to-vigorous physical activity. Concerning the development throughout childhood and adolescence, physical activity decreases on average by about 4% with each year of age after the age of six. Additionally, sedentary behaviour, which nowadays is considered not just as the opposite of physical activity but to have its own independent negative influence on health, is increasing [4, 5].

These findings underscore the need for widespread efforts to start promoting regular physical activity at an early age. However, in a recent systematic review of the effectiveness of school-based interventions, Demetriou and Höner [6] found that only 56.8% of the studies examining physical activity behaviour in children and adolescents achieved a significant – and, for the most part, small – increase. The majority of the reviewed studies suffered serious limitations. Thus, with these limitations of relevant previous studies kept in mind, further research is needed to initiate more promising and longer lasting improvements in physical activity. In the following, the most critical limitations in previous research are described and it is explained how these limitations are to be circumvented in this project.

### Lacking consideration of theoretical foundation and mediating constructs

Even though quite a few studies refer to a theoretical model (e.g., social cognitive theory, theory of planned behaviour, transtheoretical model, self-determination theory) to explain physical activity behaviour enhancement [7], very few of them explicitly design and evaluate their intervention based on the respective theory [6]. In line with the lacking consideration of theoretical models, only few studies have been carried out that systematically examine the mediating mechanisms of physical activity behaviour change in youth [8, 9]. Thus, in practice, the majority of studies have been atheoretical and to date, little information exists which allows to confirm or reject the mediating mechanisms of children’s and adolescents’ physical activity behaviour proposed by the respective models.

### Lacking consideration of moderating variables

In previous studies (e.g., HealthyPEP; 10), physical activity programmes affected boys and girls differently. Therefore, it must be taken into account that intervention effects may not be equally effective across subgroups. Rather it is important to be aware that certain preconditions might have a major influence on the effectiveness of an intervention. Thus, exploring moderating variables to determine for “whom” working mechanisms of interventions are effective is needed [10].

### Lack of intervention content information

The Consolidated Standards of Reporting Trials (CONSORT) statement for randomised trials emphasises the need to provide details of the delivery and description of the different components of the interventions [11]. Nevertheless, in most studies detailed information about the intervention content and the behaviour change techniques employed, which refer to the observable component of an intervention designed to alter causal processes that regulate behaviour, lacks [12]. Hence, a clear link between the intervention components and the changes in physical activity behaviour cannot be made [9].

## Theoretical framework

In this study, the Youth Physical Activity Promotion Model (YPAPM; 14) is taken as a basic framework (Fig. 1). Based on a social-ecological model approach [13], it suggests that the combination of both individual-level and environmental/policy-level factors can directly and indirectly influence physical activity behaviour.

**Fig. 1 Fig1:**
[figure not shown]
Youth Physical Activity Promotion Model (adapted from Welk, 1999)

The YPAPM provides a broad overview of factors associated with physical activity behaviour in children and adolescents and includes constructs that are in turn essential factors in other models. By including the constructs *perceived competence* and the social *influence of family, peers* and *teachers* the YPAPM reflects large parts of the self-determination theory [14]. According to this theory, the level of satisfaction of the basic psychological needs *competence*, *relatedness* and *autonomy* decides whether a person is *intrinsically motivated* to engage in a certain behaviour or not. Mostly cross-sectional studies have confirmed the positive influence of *intrinsic motivation* on physical activity. It is less clear though if positive changes in *intrinsic motivation* – and more precisely in the three underlying basic psychological needs – can serve as significant mediators in interventions trying to promote physical activity of children and adolescents [15]. However, there are a few longitudinal studies pointing to the promotion of the basic psychological needs as a promising means for increasing physical activity in youth. Standage, Gillison [16] showed that in a sample of secondary school students, autonomy support by the physical education (PE) teacher led to a higher satisfaction of the basic psychological needs in this specific context. The subsequently higher intrinsic motivation to participate in PE made the students participate in leisure time sports more autonomously which in turn predicted the objectively measured leisure time physical activity. In a study by McDavid, Cox [17] examining sixth graders over a period of three years, students’ satisfaction of autonomy and relatedness as well as their intrinsic motivation in the context of PE significantly predicted the development of leisure time physical activity. Finally, in a study by Chatzisarantis and Hagger [18] autonomous forms of motivation served as mediators of the effect that the promotion of the basic psychological needs by PE teachers had on adolescent students’ physical activity.

Another construct included in the YPAPM, *self-efficacy,* is the key factor in Bandura’s social cognitive theory [19]. In general, perceived self-efficacy refers to beliefs in one’s capabilities to organize and execute the courses of action required to produce given levels of attainments [19]. To date, Lubans, Foster [8] and van Stralen, Yildirim [9] have conducted two systematic reviews consisting of seven and 18 studies, respectively, that analyse physical activity intervention studies, in which a mediation analysis was carried out. The most promising mediator has been *physical activity self-efficacy*, which explicitly refers to the strength of the belief in one’s own ability to be physically active.

The social support of family and peers is another relevant factor concerning the physical activity of children and adolescents. Together with the aforementioned constructs it completes the reinforcing components for physical activity in the YPAPM. While peers seem to play an important role throughout childhood and adolescence [20], the influence of the parental support affects children’s physical activity especially until the age of 15 [21].

In short, the constructs of *intrinsic motivation*, which in turn depends on the levels of the three basic needs *autonomy*, *competence* and *relatedness* [22], as well as the constructs of *self-efficacy* [19] and *social support* hold a solid theoretical and empirical (e.g., [23, 24]) basis concerning their relevance for physical activity. The intervention programme to be presented here primarily concentrates on the promotion of the three basic needs. Concerning the conceptual similarities of competence and self-efficacy as well as relatedness and social support, the students’ self-efficacy and social support are assessed, too. Therefore, when evaluating the effects of the intervention programme it will be examined for each of these constructs if and to what extent it mediates the desired intervention effect on physical activity.

## Aims of the study

### Does the intervention programme increase the average girls’ physical activity level?

The first objective of this project is to implement and evaluate an intervention programme designed to promote 6th grade girls’ physical activity levels both during PE and outside of school. Offering modified PE classes to promote girls’ physical activity levels in PE and outside of school will be the centrepiece of the intervention. In order to reach 60 min of moderate-to-vigorous physical activity per day, recommended by the WHO [1], physical activity must take place on several occasions during the course of the day. Therefore, the intervention programme is designed to promote girls’ physical activity not only during PE lessons but also during their free time in the afternoon. PE teachers will be trained to carry out the intervention programme. This training will include guidelines and specific materials on how the prepared lesson plans should be put into practice in order to address the constructs of *autonomy*, *competence* and *relatedness,* which are in turn deemed important in terms of increasing physical activity.

*Hypothesis 1*: The intervention programme will significantly increase girls’ physical activity.

### What are the mechanisms of physical activity behaviour change in 6th grade girls?

Based on the YPAPM [25] and more specifically, the self-determination theory [22] and the social cognitive theory [19], it will be examined if positive changes in the basic psychological needs *autonomy*, *competence* and *relatedness* as well as in the adjacent constructs of *self-efficacy* and *social support* lead to an increase in *intrinsic motivation* and thereby cause the desired increase in physical activity (see Fig. 2). Additionally, it will be tested if the three basic psychological needs each have a direct influence on physical activity. Moreover, it will be examined if positive changes in *self-efficacy* and *social support* lead to an increase in physical activity in addition to the increase produced by *intrinsic motivation* and the underlying basic psychological needs.

**Fig. 2 Fig2:**
[figure not shown]
Model of the mediating mechanisms of physical activity to be examined in this project

To this end, several consecutive hypotheses are made.

*Hypothesis 2a*: By following the elaborated lesson plans, the trained teachers will be able to *support girls’ autonomy, competence* and *relatedness* during PE.

*Hypothesis 2b*: The teachers’ support of these potential mediators will result in higher *satisfactions in girls’ autonomy, competence* and *relatedness* in the context of PE.

*Hypothesis 2c*: This will give rise to higher satisfactions of the respective constructs as well as of the constructs *self-efficacy* and *social support* in the leisure time context.

*Hypothesis 2d*: The higher levels of satisfaction of the three basic psychological needs will lead to higher levels in the girls’ intrinsic motivation towards physical activity.

*Hypothesis 2e*: Changes in at least one of the constructs *autonomy*, *competence*, *relatedness*, *self-efficacy*, *social support* and *intrinsic motivation* in the leisure time context significantly mediate the positive effect of the intervention programme on the girls’ physical activity levels.

### Do socioeconomic status, BMI, environment and/or teacher moderate the intervention effect on physical activity?

Based on the theoretical framework of the YPAPM, it will be examined whether socioeconomic status, BMI, environmental factors and/or the girls’ impression of their PE teacher have a moderating effect on the intervention effect.

*Hypothesis 3*: Socioeconomic status, BMI, environment and/or teacher characteristics influence the effect of the intervention programme on the girls’ physical activity.

## Methods/design

### Study design

The study design adheres to the CONSORT guidelines [11]. The effects of the intervention programme will be examined in a two-arm cluster randomised controlled trial with one intervention group and one waiting control group. The intervention programme is carried out during the regular PE lessons by the respective teachers. The *control group* receives regular PE lessons. After follow-up data assessment, the control group receives the intervention programme. The intervention programme is carried out for five months followed by a three-month follow-up period within one school year.

The majority of variables (physical activity; support and satisfaction of autonomy, competence, relatedness in context of PE and leisure time; intrinsic motivation; self-efficacy; social support) is assessed at three time points: baseline (T1), post-intervention (T2) and follow-up (T3) (see Fig. 3). Socioeconomic status, BMI, teacher characteristics and environmental factors are measured only at baseline. Additionally, in order to monitor to what extent the intervention programme is actually implemented by the respective teachers during the main study, a process evaluation will be carried out. (see Additional file 1: Table S1).

**Fig. 3 Fig3:**
[figure not shown]
Study design

### Study sample

The study sample consists of 6th grade girls (11–13 years of age) from lower secondary schools in and around the city of Munich, Germany. This study sample has been chosen for the following reasons:Behaviour patterns are less definite in young adolescents than in adults and can be more easily altered [26]. Additionally, compared to children, young adolescents have the capability to make decisions about their behaviour on a higher cognitive level, which is a prerequisite for the intervention programme to work.The results of previous projects indicate differing effects of a school-based health promotion physical activity programme on girls and boys [27, 28]. Therefore, in this study we focus on girls, who are the population most in need for physical activity promotion programmes due to their low physical activity levels [4]. Additionally, in Bavaria PE classes normally are separated by gender and therefore, from a practical perspective it is hardly possible to consider boys and girls in the same classes at the same time.The setting of lower secondary schools has been chosen because here, the percentage of students from lower socio-economic status groups is higher compared to the other secondary schools in Germany [29]. The physical activity levels of children and adolescents, and especially girls from a low socioeconomic background, are particularly low [30, 31].

### Sample size calculation

The sample size needed to detect the intended increase in physical activity from baseline to post-intervention was calculated using the formula by Rutterford, Copas [32], who consider several aspects of cluster randomisation, e.g., the intended effect of the intervention, the estimated intracluster correlation (ICC), potentially variable cluster sizes and the implied levels of significance and power. To include appropriate figures for the respective parameters, it is referred to previous research. An intervention-based increase of twenty minutes per day of moderate-to-vigorous physical activity is estimated based on the systematic review by Camacho-Minano, LaVoi [33]. An ICC at the class-level of 0.1 appears appropriate based on the study by Lonsdale, Rosenkranz [34]. Additionally, to account for variable cluster sizes (i.e. number of students within the respective classes) in the present study, we estimate a variation coefficient of the cluster size of 0.25. By inserting the specified figures for the respective parameters and setting an alpha of 0.05 and a power level of 80%, a sample size of at least 467 is required to detect the intended baseline-intervention change in physical activity. Finally, taking dropouts into consideration a sample size of 600 is sought.

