### Randomisation

Randomisation of the study sample in intervention group and control group takes place on the school level and is done before pre-test data assessment by a researcher of the study team (see Fig. 3). A computer-based random number producing algorithm is generated and completed by an independent researcher to ensure an equal chance of allocation of a school to either group. No matching is undertaken. Factors differentiating between classes or schools are compensated by use of a multilevel analysis (see statistical analysis).

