### Statistical analysis

Structural equation modeling in R will be used to examine the scientific questions outlined above. To evaluate the effect of the intervention, a multiple group analysis with the intervention and control group will be performed. To account for the clustered nature of the study sample, physical activity will be included in four levels. Level 1 will be the repeated measurements for each individual, level 2 will be the individual itself in which the repeated measurements are nested. Level 3 stands for the class the individual is part of. The class is again nested within a certain school, which represents level 4. The basis for this approach is the assumption, that physical activity is not only influenced by the individual’s personal attitudes and preferences but also by the attitudes and behaviour of the class teacher as well as by the school environment. In a further step, the model will be explicitly extended by the potential moderators BMI, socioeconomic status as well as characteristics of teacher and environment to check if they exert a significant influence on the effect of the intervention.

To gain a deeper insight into the mechanisms of physical activity behaviour change, the girls’ physical activity will be regressed onto the potential mediators. This way, it can be examined which mediators are of incremental importance in relation to the other mediators included in the model concerning the promotion of physical activity. Thereby, the assumed mediators will each be included in three levels.

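### The sample size is built on classes although schools are randomised, so 467 girls give less than 80% power if schools supply several correlated classes

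*Protocol article*

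**What the plan says.** Three sections of the protocol article bear on this point.

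- **Sample size calculation.** The clustering inputs are all at class level: "An ICC at the class-level of 0.1 appears appropriate", and cluster size is explained as "variable cluster sizes (i.e. number of students within the respective classes". For its spread, "we estimate a variation coefficient of the cluster size of 0.25". The target is 20 minutes per day of moderate-to-vigorous activity, with alpha 0.05 and 80% power. The result is 467 girls, raised to 600 for dropouts.
- **Randomisation.** "Randomisation of the study sample in intervention group and control group takes place on the school level".
- **Statistical analysis.** A four-level model has repeated measurements within girls, girls within classes, and then: "The class is again nested within a certain school, which represents level 4". The reason given is that both the class teacher and the school environment are assumed to affect activity.

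**The concern.** When whole schools are allocated, all participating classes of a school fall into the same arm. The variance of the difference between arms then contains two clustering terms: the correlation between girls in the same class, and the correlation between girls in different classes of the same school. A design effect built on classes alone sets the second term to zero. The article does so when sizing the trial, yet justifies its analysis model by assuming a school influence.

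What is at stake is the article's only stated power justification, which bears on Hypothesis 1. If the true power is clearly below 80%, a null result could be read as an ineffective programme when the trial was too small to tell.

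**Working it through.** **Inputs from the article.** Class ICC 0.1; coefficient of variation (CV) of class size 0.25; alpha 0.05 (two-sided assumed, since the side is not stated); power 80%; N = 467, raised to 600.

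**Inputs the article does not give.** The SD of activity, girls per class (m), classes per school (k), and the correlation between girls in different classes of the same school (rho_s). The values of m, k and rho_s below are assumptions.

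**Step 1: can 467 be reproduced?** No, because it depends on the SD and m. Back-solving N = 4 × (1.96 + 0.842)² × SD² / 20² × DE for 467 gives an SD of about 55, 49 or 44 min/day at m = 10, 15 or 20. So 467 is taken as correct for the class-only calculation and then scaled. The SD cancels in that scaling.

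**Step 2: class-only design effect.** DE_class = 1 + ((1 + CV²)m − 1) × 0.1. With m = 15: 1 + (1.0625 × 15 − 1) × 0.1 = 2.49.

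**Step 3: design effect with schools as the randomised unit.** DE_school = DE_class + m(k − 1) × rho_s. The 0.1 is read as the full correlation within a class, including any school share. This reading is kind to the plan, because one class per school then costs nothing. With m = 15, k = 2 and rho_s = 0.05: 2.49 + 15 × 1 × 0.05 = 3.24.

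**Step 4: consequences.** Required N = 467 × DE_school / DE_class, rounded up. Power at 467 = Φ((1.96 + 0.842) × √(DE_class / DE_school) − 1.96). For 600 girls, the first term is multiplied by √(600/467).

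Results for m = 15:

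| k | rho_s | DE | Power at 467 | N for 80% | Power if all 600 are analysed |
|---|---|---|---|---|---|
| 1 | any | 2.49 | 80% | 467 | 88.8% |
| 2 | 0.01 | 2.64 | 77.7% | 496 | 87.0% |
| 2 | 0.02 | 2.79 | 75.4% | 524 | 85.1% |
| 2 | 0.05 | 3.24 | 69.0% | 608 | 79.5% |
| 3 | 0.01 | 2.79 | 75.4% | 524 | 85.1% |
| 3 | 0.02 | 3.09 | 71.1% | 580 | 81.4% |
| 3 | 0.05 | 3.99 | 60.0% | 748 | 70.9% |

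Over m = 10 to 20, k = 2 to 3 and rho_s = 0.01 to 0.05, power at 467 runs from 78% down to 58%, and N for 80% from about 491 to 776.

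**Step 5: the dropout margin.** Going from 467 to 600 allows for 1 − 467/600 = 22.2% loss. If 496 are needed, 600 allows 1 − 496/600 = 17.3%; if 524 are needed, 12.7%; if 608 are needed, nothing is left.

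These are normal approximations. A small number of schools would cost some further power through the degrees of freedom.

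**The case against.** **The analysis model already includes the school.** This is true, and it means that no bias or inflated type I error is shown. A reader might infer from the mismatch that the analysis itself is invalid; the article does not support that. But a school level in the model only puts the school variance into the standard error. It does not supply the girls or schools needed to keep 80% power.

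**The size of the loss is assumed, not documented.** This stands. Classes per school, class size and the between-class correlation are all unstated. With one class per school, or with no correlation between classes of a school, the loss vanishes in this approximation. A reader might infer that power is as low as 50 to 60%. Figures in that range need three or more classes per school or a high correlation, and the article establishes neither.

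**The trial is powered for a change from baseline to post-intervention.** A stable school difference, equal at both times, cancels from a change. The relevant correlation is that of the change, or of the baseline-adjusted outcome, and it may be smaller than that of activity level. The article does not say which quantity its 0.1 describes. This argues for choosing the ICC carefully, not for omitting the school term.

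**The target of 600 provides a margin.** The article assigns that margin to dropouts. A reader might infer that school clustering consumes all of it. At the lower end of the illustration it does not: with 524 needed, about 13% dropout is still covered.

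**No calculation error is shown.** This is also correct. Because 467 cannot be reproduced, the fault lies in the unit used for planning and not in the sums.

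**Conclusion.** The point holds in a conditional form. It is certain from the text that schools are randomised while the calculation treats the class as the cluster, and that the article itself assumes a school influence. The 80% at 467 girls is therefore right only if each school gives one class or if classes of the same school are uncorrelated on the analysed quantity. Modelling class and school as separate levels suggests that several classes per school are expected, at least in some schools, but the article does not say so.

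Under any other conditions power is below 80%, by an amount the article does not allow one to fix. With 15 girls per class and 2 classes per school, the loss ranges from about 2 percentage points (correlation 0.01) to 11 (correlation 0.05), and it is larger with 3 classes. Confidence is high for the mismatch and its direction. The power figures are illustrations.

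**What to change.** Recompute the sample size with the school as the randomised cluster: DE = 1 + ((1 + CV²)m − 1) × ICC_class + m(k − 1) × ICC_school. Here k is the actual number of classes per school, and ICC_school is the correlation between girls in different classes of one school. State the SD, class size, classes per school and number of schools used.

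Both ICCs should refer to the analysed quantity, that is the change or the baseline-adjusted outcome. ICCs of activity level at T1 alone would not serve. They can come from external sources or from wave 1 data pooled without using arm. Pooled change data carry any treatment difference into the school component, which would tend to raise it, so a sensitivity range is needed in either case. Then restate the power that 467 and 600 girls give, and how much dropout 600 still covers.

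The cost is one recalculation, largely from data in hand since wave 1 is complete, and possibly a less favourable stated power. Spreading the remaining recruitment over more schools would recover some power for the same number of girls, but it is optional. It means more school contacts and teacher trainings, and schools with a single class cannot help to separate the class and school levels of the model.
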